## Abstract

**Background:**

People bereaved by drug overdose experience a “special grief” that includes guilt, shame, and blame for their loved one’s death, which often compounds suffering and interferes with help-seeking. This population is vulnerable to poor health outcomes including prolonged grief disorder, risky substance use, and suicidal thoughts and behaviors. Peer grief support may reduce risks in people bereaved by overdose by buffering grievers from the negative effects of increased stigma and isolation. Peer Support Community Partners has developed the RIVER peer grief support model for bereavement. The model has been implemented successfully in the community and for drug overdose bereavement, but has not yet been rigorously tested.

**Methods:**

The current study is a two-phased project that aims to test whether the RIVER peer grief support approach improves health outcomes in those grieving drug overdose deaths. In the first phase, we will prepare for and conduct a pilot test of the RIVER peer grief support approach. We will also assess an innovative mechanism for engaging grievers through Medical Examiners Offices (MEOs). In the second phase, we will compare enhanced usual care (EUC) to EUC plus RIVER peer grief support (RIVER) in a randomized controlled trial.

**Conclusions:**

The study aims to build the science of overdose bereavement and provide increased support for a vulnerable population of grievers.

**Trial registration:**

https://clinicaltrials.gov/study/NCT06854757 (02/25/2025).

## Introduction

The United States (US) is in an overdose crisis. An estimated 110,000 Americans died by drug overdose in 2023 [1], putting the national total since 2000 at more than 1.1 million overdose deaths [2]. Overdose death rates have accelerated as the crisis wears on and as more deadly drugs such as fentanyl make their way into the drug supply [3]. The overdose crisis has had profound, negative effects that extend beyond the tragedy of the deaths themselves. For example, the overdose crisis has increased the burden on health, foster care, and criminal-legal systems [4] and spurred on syndemics [5] of suicide [6], infectious disease [7], and violence [8, 9]. Research has focused on the broad effects of the overdose crisis on society but has neglected the impact on people who are left behind by drug overdose deaths and the potential role that overdose bereavement may play in fueling risky substance use among the bereaved [10].

Recent findings highlight it is common for people to lose someone to overdose. About 42% of people in the US (i.e., more than 125 million people) personally know someone who died by overdose [11]. More than 32% of adults report that they have lost a loved one to an opioid overdose [12]. Children have also been heavily impacted by overdose loss. In 2019, more than 1.4 million US children lost a family member to overdose, including 317,000 who lost a parent [13]. To put these data into perspective, the prevalence of exposure to overdose deaths is estimated to be more than three times higher than the prevalence of exposure to suicide [14] and is on par with rates of bereavement by COVID-19 deaths [15]. Without intervention, the ripple effects of overdose loss will persist, affecting millions of individuals and communities.

People who are bereaved by overdose are vulnerable to poor mental health outcomes. They experience high rates of prolonged grief disorder (PGD) [16, 17], a type of grief that lasts longer and has more severe effects than other types of grief [18]. Rates of PGD are higher among those bereaved by overdose compared to those who have lost someone to suicide, homicide, and other unintentional injuries [19]. Overdose bereavement is also associated with the development of posttraumatic stress disorder, depression, anxiety, physical pain [20], as well as suicidal thoughts and behaviors [17, 21–23].

People who experience grief, particularly prolonged grief, are at increased risk for developing their own substance use problems [24–26], perhaps because they struggle to emotionally process and accept the loss [27] or because they use substances to cope. Substance use may fuel substance-related morbidity and mortality among the bereaved by leading some to initiate substance misuse and others to experience increases in the severity of their substance use disorders. Although no research has evaluated the association between overdose bereavement and a subsequent overdose among the bereaved, a study of Norwegian parents who lost children to overdose revealed these grievers were at more than double the risk for external injury deaths (i.e., accidents, suicides, or homicides) [28]. Studies focused on bereaved PWUD show an increased risk for their own experiences of non-fatal or fatal overdose [27, 29]. Overdose bereavement may perpetuate the overdose crisis by increasing risk for overdose morbidity and mortality in people left behind.

The traumatic nature of loss and stigma associated with overdose may make healing from grief more difficult [16, 30]. The Dual Process Model of grief suggests that healing can occur when grievers balance both processing the loss and restoring their lives after loss [21, 30]. People bereaved by overdose may struggle to emotionally process and accept the loss due to intense, negative emotions, including shame and guilt [10, 16, 31–33]. Some may also struggle to accept the loss if there is ambiguity surrounding the circumstances of the death or confusion about whether the overdose was suicidal or homicidal in nature [21, 34]. Research comparing overdose bereavement to other traumatic losses shows that guilt and shame are significantly more severe among people bereaved by overdose than among people bereaved in other ways (e.g., a cancer-related death) [10, 16, 32, 35]. Stigma may be especially common and harmful to people with personal and family histories of drug use [32, 36]. The experience of stigma and intense emotions interfere with meaning making and healing after loss [21] and may contribute to mental health conditions such as depression [17, 31]. Addressing the intense negative emotions that inhibit acceptance of the loss and the experiences of stigmatization may help people bereaved by overdose heal.

People bereaved by overdose are in critical need of resources as they often lack support for restoring their lives after loss [37]. Informal social support from friends and family appears to be a critical component of healthy grieving by promoting the restoration of the lives of bereaved people [37]. Unfortunately, perceived stigma interferes with healing by promoting social withdrawal and negatively impacting the relationships of people bereaved by overdose [32, 38–40]. People bereaved by overdose, especially bereaved PWUD, also face barriers to engaging with professional supports [27]. While most people bereaved by overdose report that they would benefit from professional help, only one-third report they have received it [41]. In the absence of informal and professional support, it can be difficult for those bereaved by overdose deaths to effectively cope with the loss.

Peer grief support interventions may be protective against PGD, substance use, and mental health outcomes. Peer interventions involve “giving and receiving help founded on key principles of respect, shared responsibility, and mutual agreement” [42]. A review found that peer support was associated with reductions in risk for PGD and with improved well-being in people bereaved by sudden or violent deaths [43, 44]. Importantly, people who receive peer grief interventions experience reductions in substance use compared to grievers who do not receive peer support [45–47]. Qualitative studies of this population suggest that peer interventions may serve as an antidote to the trauma and stigma of overdose bereavement by promoting connectedness, acceptance of the loss, and adaptive coping [39, 48]. Research also demonstrates that peer-facilitated interventions can improve outcomes for the facilitators themselves evidenced by greater posttraumatic growth, increased social connectedness and reduced adverse grief outcomes in those facilitating a peer grief intervention [49, 50]. However, the evidence supporting peer grief support interventions for overdose bereavement is scarce. To our knowledge, no peer reviewed research has evaluated the effectiveness of peer interventions for preventing PGD and substance misuse in people who are bereaved by overdose.

To address this gap, researchers from academic institutions have collaborated with a peer grief support organization [i.e., Peer Support Community Partners (PSCP)] in the current study to advance the science of overdose bereavement. PSCP has developed and implemented a peer grief support model called RIVER (relate, invite, validate, empower, reassure) for people bereaved by overdose. The RIVER model (Fig. 1) was developed by people who experienced traumatic bereavement, including bereavement by overdose, after decades of learning from and delivering peer grief support. The RIVER model distills this learning, evidence-based peer support practices, and trauma-informed approaches. Rather than prescribing specific intervention activities, the RIVER model of peer grief support guides peer grief allies, or supporters in *how* to engage with people bereaved by overdose. Peer grief allies are trained to use their lived experience to *relate* to people who are bereaved by overdose, *invite* them to make meaning of the loss by sharing their grief story and demonstrating that their story is welcome, *validate* their grief to show that their reactions are understandable, *empower* grievers to engage in restorative coping so that they can restore their lives after loss, and *reassure* them grief is a lifelong journey and process. While the RIVER peer grief support model was developed without specific attention to the Dual Process Modelof coping with grief, RIVER closely aligns with the model because RIVER promotes balancing both loss- and restoration- related bereavement needs. This study will be the first to test the impact of the RIVER peer grief model on grief, substance use, and mental health outcomes of people bereaved by overdose.

**Fig. 1 Fig1:**
[figure not shown]
RIVER peer grief support model

To address evidence that most grievers lack access to grief support, this study established partnerships with Medical Examiners’ Offices (MEOs). MEOs are legally mandated to conduct death investigations following every overdose death and to make death notifications to the legal next-of-kin to those who die by overdose. As part of the death investigation and notification process, MEOs routinely interact with the next-of-kin to overdose decedents. Indeed, MEOs may be the only organizations that systematically compile the contact information of all next-of-kin to overdose decedents within their jurisdictions. Partnering with MEOs may provide a scalable path to proactively engage people bereaved by overdose before they develop poor grief-related outcomes. This study will be the first to evaluate the feasibility, acceptability, and appropriateness of proactively engaging people bereaved by overdose via MEOs.

## Study aims

The current study has three aims. In aim one, we will adapt training materials for the RIVER peer grief support model to fit the needs of the communities surrounding our partnering MEOs, develop a fidelity measure, and create workflows for engaging grievers and connecting them with peer grief allies. In aim two, we will conduct a pilot test to evaluate the acceptability and feasibility of engaging grievers via MEOs, refine the fidelity measure, and evaluate if peer grief support using the RIVER model was satisfactory to grievers. In aim three, we will conduct a randomized controlled trial (RCT) to evaluate the effectiveness of the RIVER peer grief approach plus enhanced usual care (RIVER + EUC) to prevent PGD and substance misuse in people bereaved by overdose, over and above any effects of EUC. Participants will be recruited from MEOs and will complete baseline, 3, 6, and 12-month surveys on (a) proximal outcomes (i.e., connectedness, acceptance, and coping) and (b) long-term outcomes (i.e., PGD and substance misuse). Post-RCT qualitative interviews of study participants and mixed methods assessments with peer grief allies will supplement data collection and allow us to understand the characteristics of the RIVER peer grief approach that drive effectiveness and its impact on peer grief allies.

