## Methods

### Overview of study procedures

First, we will supplement the already-developed RIVER peer grief approach with materials needed to rigorously test its effectiveness (Aim 1). We will engage three advisory boards (family, research, and medical examiners) to (1) develop recruitment materials and procedures for recruiting grievers who interact with MEOs (2), adapt RIVER training materials to local MEO regions, and (3) develop fidelity measures. Next, we will conduct a pilot test of the RIVER peer grief support model with at least twenty people who are bereaved by a drug overdose death and recruited through MEOs. We will determine the feasibility and acceptability of griever engagement procedures, as well as grievers’ satisfaction with RIVER peer grief support (Aim 2).

In our third aim, we will use an RCT to test the effects of RIVER plus EUC compared to EUC alone for people who are bereaved by a drug overdose death and recruited from MEOs (Aim 3). People bereaved by a drug overdose death will be randomized to receive RIVER plus EUC or the EUC alone condition. RCT participants (*N* = 320 at baseline; 208 at 12-month follow-up) will be assessed on their experience of proximal and distal grief, substance use, and mental health outcomes at baseline, and during 3-, 6-, and 12-month-follow-ups. We will also conduct qualitative interviews with a subset of participants at the end of the study to contextualize the mechanisms in which the RIVER model affected them. Finally, we will collect qualitative and quantitative data from peer grief allies at the beginning and end of the RCT to explore how delivering peer grief support affects their well-being.

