Three months after baseline, the study team will conduct 45-minute interviews with the participant. Participants will complete the Feasibility Intervention Measure (FIM) [56] that tests whether an intervention can be successfully used or carried out within a given setting. The FIM includes questions about how workable, possible, doable, and easy the RIVER peer grief support model was for the participant. Acceptability will be evaluated using the Acceptability of Intervention Measure [56] that tests how agreeable, palatable, or satisfactory the intervention was. Finally, we will use the Client Satisfaction Questionnaire (CSQ) [57, 58] where scores of at least 26 of 32 (81%) indicate acceptability of an intervention [59]. Questions include whether the intervention was a quality service, met their needs, and helped them cope. Participants will be asked open-ended questions about their experience with recruitment (e.g., “What did you like or not like about that process?”) and peer grief support (e.g., “What did you think of your discussions with your peer grief ally? How can we make the discussions helpful to people from different backgrounds?”). Interviews will be recorded and transcribed. Participants will be compensated $50 at baseline and $75 at the follow-up interview.

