**RIVER Feasibility, Acceptability, and Satisfaction (Aim 2)**		
Feasibility	Extent of how workable, possible, doable, and easy RIVER was	Feasibility Intervention Measure (FIM)
Acceptability	Extent of how agreeable, palatable, or satisfactory RIVER was	Acceptability of Intervention Measure
Satisfaction	Assesses RIVER on quality, needs met, and helpfulness	Client Satisfaction Questionnaire

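### Aim 2 asks whether engaging grievers through medical examiners is feasible and acceptable, but the only named feasibility and acceptability scales rate RIVER, so that question is answered only in part, and probably favourably

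*Protocol article*

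**What the plan says.** The objective appears in three places in the protocol article.

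- **Study aims:** "we will conduct a pilot test to evaluate the acceptability and feasibility of engaging grievers via MEOs". The same sentence adds work on the fidelity measure and asks whether RIVER satisfied grievers.
- **Overview of study procedures:** "We will determine the feasibility and acceptability of griever engagement procedures", again with satisfaction as the question about RIVER.
- **Introduction (paragraph on MEO partnerships):** "This study will be the first to evaluate the feasibility, acceptability, and appropriateness of proactively engaging people bereaved by overdose via MEOs". This adds a third property, appropriateness.

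The measures are in Aim 2 procedures and Table 1.

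- **FIM:** "The FIM includes questions about how workable, possible, doable, and easy the RIVER peer grief support model was for the participant". Table 1 has "Extent of how workable, possible, doable, and easy RIVER was".
- **Acceptability of Intervention Measure:** a scale "that tests how agreeable, palatable, or satisfactory the intervention was". Table 1 has "Extent of how agreeable, palatable, or satisfactory RIVER was".
- **Client Satisfaction Questionnaire:** rates the service received.
- **Open-ended questions:** cover recruitment as well as peer support.

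All of these are collected at an interview three months after baseline, with enrolled participants. Aim 2 analyses lists engagement as an item separate from feasibility, acceptability and satisfaction, to be summarised by rates or means. It also plans to code interview comments on how feasible and acceptable recruitment was.

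**The concern.** The aim is about a recruitment route, while the scales that carry the aim's two key words are about the support delivered afterwards. A participant can value a peer ally highly and still have found the approach from the medical examiner intrusive, or the reverse. A score on one does not measure the other.

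The respondents are also selected on something close to the answer. A person reaches the three-month interview only after agreeing to be contacted, being reached, passing screening, consenting, being referred to RIVER and staying three months. Next-of-kin who disliked the approach are likely to have left at the first step. Those who remain are asked about that first contact after they have been offered RIVER sessions, which may colour the recollection.

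At stake is how firmly the study can support its statement that proactive engagement through MEOs is acceptable. The Introduction presents that route as possibly scalable, and scalability concerns everyone approached, not only those who enrol.

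**Working it through.** Aim 2 is descriptive and single-arm, with 20 participants planned and the final number set by thematic saturation. There is no power or precision figure to reproduce. The check sets objective, measure and respondent side by side.

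| Question about MEO engagement | Named scale that rates it | Other source in the plan | Who supplies it |
|---|---|---|---|
| Feasibility | None (the FIM rates RIVER) | Engagement rate; coded recruitment comments | The rate can include refusers if it counts everyone approached; comments come from enrollees |
| Acceptability | None (the acceptability scale rates RIVER) | Coded recruitment comments | Enrollees at three months |
| Appropriateness | None | None described | Nobody |

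Reading across:

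1. *Object.* Both objective statements attach feasibility and acceptability to engagement, and satisfaction to RIVER. Table 1 attaches all three to RIVER. This is a stated mismatch, not an omitted detail.
2. *Feasibility* can be answered from counts of people approached and enrolled.
3. *Acceptability* can be answered only for those who accepted. A rate shows how many declined, not whether they found the contact unacceptable or declined for another reason.

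How little acceptors' answers say about everyone approached can be bounded without assuming anything about non-enrollees. Let *f* be the share of those approached who enrol and *a* the share of enrollees who find the contact acceptable. Acceptability among all approached lies between *f·a* (no non-enrollee favourable) and *f·a* + (1 − *f*) (all favourable). The documents give neither quantity, so these are assumed values with *a* = 0.90:

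- *f* = 0.20 (20/0.20 = 100 approached): 0.18 to 0.18 + 0.80 = 0.98
- *f* = 0.50 (40 approached): 0.45 to 0.45 + 0.50 = 0.95
- *f* = 0.80 (25 approached): 0.72 to 0.72 + 0.20 = 0.92

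The width is 1 − *f* whatever *a* is. These are limits of what could be excluded, not estimates of bias.

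An engagement rate over everyone approached is estimable from the same pilot. Taking the number approached as fixed, 20 of 100 has an exact 95% interval of 12.7% to 29.2%, and 20 of 40 has 33.8% to 66.2%.

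**The case against.** The best reply is that the plan does not rely on the scales for the MEO question. Aim 2 analyses treats engagement as its own quantity, provides for coding of recruitment comments with a second coder verifying, allows for negative comments, and even gives helpful MEO outreach as an example theme. For about 20 people, with sample size set by saturation, a mixed-methods answer is defensible. Table 1 labels its scales openly as RIVER scales. The article does not say over whom the engagement rate is taken, but a condensed article may leave that to the full protocol, so the gap is not an error. Appropriateness is one word in the Introduction and is not part of Aim 2 as stated under Study aims.

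Much of this stands, and it rules out stronger readings.

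- A reader might infer that the pilot cannot answer its aim. It can in part, through the engagement rate and the recruitment interviews.
- A reader might infer that the result is bound to look good. A low engagement rate would look poor, so the favourable direction is probable for the interview evidence only.
- A reader might infer that the decision to use MEOs in the 320-person trial hangs on these scores. Study aims and Aim 3 procedures already fix MEO recruitment, and no go/no-go rule is tied to the scales.

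What the reply does not remove is that the two instruments named for feasibility and acceptability address a different object from the aim, and that every described interviewee is an acceptor.

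**Conclusion.** The point holds as a mismatch between objective and instrument, with a selected set of respondents. Feasibility of MEO engagement can be answered if the engagement rate counts everyone approached. Acceptability is answered only for enrollees, by open-ended questions three months later, and probably favourably. Appropriateness is promised in the Introduction and measured nowhere in the article.

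No size can be put on the bias, because the documents give neither uptake nor any acceptability figure. The favourable direction rests on one assumption: that people who disliked the approach were more likely to decline it. It is a change worth making, because the remedy is small and lets the pilot speak to its own stated aim. It does not undermine the pilot's other purposes or the design of the RCT.

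**What to change.** 1. Give the FIM and the Acceptability of Intervention Measure at the baseline interview too, with being contacted about the study through the MEO as the thing rated. Baseline precedes referral to RIVER, so support experience cannot colour the answer. Keep the three-month RIVER ratings as they are. Aim 2 procedures allow someone other than the approached next-of-kin to enrol, and allow grievers to contact the team themselves, so record whether the respondent was the person the MEO approached.
2. State that these scores and the recruitment interviews describe people who accepted contact and enrolled.
3. Make the engagement rate already planned in Aim 2 analyses the main feasibility result, with all next-of-kin approached by the MEO as denominator.
4. Either rate appropriateness at the same baseline interview or remove the word from the Introduction.

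The cost is a few more items on a baseline contact already planned, counts from the MEO consent-to-contact step, and possibly a less favourable headline. The change does not remove selection by refusal: the views of those who declined remain unmeasured, and the report should say so.
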